The study design for this nutritional intervention protocol is a randomized, double-blind, placebo-controlled, crossover study. There are two arms to the study, (1) an investigational formulation period followed by a placebo formulation period, or (2) a placebo formulation period followed by investigational formulation period. Each patient will receive both the investigational formulation and the placebo formulation, with a washout period between each arm. The randomization schedule was created by the Investigational Drug Service Pharmacy using randomization software in a 1:1 ratio with a block size of 4. Participants are enrolled in the next open slot of on the randomization table. The nutritional formulations are coded by the manufacturer lot number and, therefore, the clinical staff is blind to the actual contents of the container (active verses placebo).

Once randomized, subjects start Intervention Period 1, a 4-week period in which they receive nutritional formulation containing BHB or placebo while maintaining the diet noted at entrance into the study. Home monitoring occurs as indicated in Fig. 1. After 4 weeks of blinded intervention, subjects are evaluated in the clinic and then cease consumption of the ketone formulation or placebo for 4-week washout period. Following completion of the washout, subjects enter a second 4-week period in which they receive formulation versus placebo. They will continue the home monitoring throughout the duration of the study. Subsequently, at the completion of the second intervention, they undergo the final scheduled study visit and laboratory sampling. A washout period follows Intervention Period 2, and at approximately week 16 of the study, a follow-up call is made to the family to review symptoms and ensure the patient is not experiencing adverse events during this period. The trial schedule of enrollment, interventions, and assessments is outlined in Fig. 1 (FANS trial schedule of procedures).

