No studies testing ketone supplementation in patients with AS exist. Therefore, sample-size estimation is based on measures of ketosis. It is assumed from murine pre-clinical investigations, non-AS clinical studies using MCT and/or BHB, and low-carbohydrate dietary interventions, that the minimal change of the secondary outcome, degree of ketosis, from the baseline to the end of the fourth week of the investigational formulation intervention period will be 100% change from baseline (baseline for standard diet is typically < 0.5mmol/L of d-BHB in blood, or < 5 mg/dL acetoacetate in urine). The acetoacetate test used is Ketostix (Bayer Corp. Diagnostics Division, Tarrytown, NY, USA) which exhibits a sensitivity of 78% and a specificity of 96% when compared to a serum standard of 14.4 ml/dL. Considering a 25% drop-out rate, an estimate of 25 subjects need to be screened to achieve 15 completers.

Descriptive statistics, such as mean and standard deviation, are used to describe continuous variables, and frequency for the categorical variables. Means are compared using a paired two-sample *t* test. Statistical significance for all tests is *p* < 0.05. Multiple comparisons can be made including: (1) each subject to serve as their own control, comparing investigational formulation to placebo formulation, as well as to baseline, (2) each dietary background group considered in aggregate, comparing investigational formulation to placebo formulation, as well as to baseline, and (3) all subjects considered in aggregate, comparing investigational formulation to placebo formulation, as well as to baseline.

Any patient who receives the study formulation for any amount of time will be included in the intent-to-treat population for study analyses. Missing data points in this population will be addressed in discussion of any published results. Data from protocol-compliant participants is the defined population for efficacy subset analyses; any participant who received both protocol-required formulations and all required clinical assessments is considered protocol compliant. Such an efficacy subset analysis will be the primary approach for determining whether the trial endpoints are met. Those patients who complete the baseline visit, but do not start Intervention Period 1 and are withdrawn from the study, will be used for natural history reportable data only but will not be included in analyses for determining whether the outcome measures of the trial have been met.

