The animal evidence supporting ketone supplementation and the clinical evidence for KDs in models of AS and seizure control, respectively, suggest that dietary interventions including exogenous ketones may be an important development in clinical management strategies. The current study is designed as an initial evaluation of ketogenic formulations used with a variety of dietary backgrounds. It represents a unique opportunity to study the potential benefits of nutritional intervention in a pediatric population (ages 4–11 years) with AS. The knowledge gained from the study may guide further evaluations in the use of exogenous ketones for nutritional strategies in the dietary management of patients AS.

It is known in the AS population that there is a large placebo effect. Our study also offers a unique design in which the use of objective measures is prioritized. We hope that this will yield measures that benefit future trials in the Angelman community in addition to a clearer understanding of the overall effectiveness and mechanism of action of BHB for inducing ketosis. The ultimate goal will be to positively impact nutritional status, which should enhance the ability of the patient to overcome the symptoms of AS such as seizures, cognition and learning, gait/mobility, and/or sleep disturbances.

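### The named paired t test ignores period in a randomised two-sequence crossover; if a period effect exists, the likely cost is lost power, with material bias only if completion is also uneven

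*Protocol article*

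**What the plan says.** The Study design section describes a two-period crossover with two randomised sequences: "1) an investigational formulation period followed by a placebo formulation period, or (2) a placebo formulation period followed by investigational formulation period". The allocation list was made "using randomization software in a 1:1 ratio with a block size of 4". Between periods children "cease consumption of the ketone formulation or placebo for 4-week washout period".

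The Statistical considerations section names one method for comparing means: "Means are compared using a paired two-sample" t test, at a single 0.05 level. It is to serve three sets of comparisons: within subject, by dietary background, and "all subjects considered in aggregate, comparing investigational formulation to placebo formulation, as well as to baseline". Nothing in the article mentions a period effect, a sequence term or a crossover model.

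The same section makes the protocol-compliant children the primary analysis set, meaning those who had both formulations and all required assessments. It aims for 15 completers and allows for 25% drop-out. The Study design section sets no required number of children per diet.

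**The concern.** A paired t test pools the two sequences as if order did not matter. In a two-period crossover each child's formulation-minus-placebo difference also contains the change from period 1 to period 2, with one sign in one sequence and the opposite sign in the other. Two things can follow if such a change exists:

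- The opposite shifts act as extra scatter between children, so the standard error is too large and power is lost.
- If the two sequences have unequal numbers of completers, the shifts do not cancel, and part of the period effect is counted as formulation effect.

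With only about 15 completers, neither loss is easily absorbed. The article fixes the test by name, so this is a stated choice that does not match the stated design, not a detail left for later.

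**Working it through.** **Inputs from the article.** Two sequences, 1:1 in blocks of 4 (Study design); paired t test at 0.05, 15 completers, 25% drop-out (Statistical considerations). The test is taken as two-sided because sidedness is not stated.

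**Inputs that are assumptions.** The article gives no SD, no power and no period effect. The SD of the within-child difference is therefore set to 1, the formulation effect to 0.78 SD (which gives the paired test 80% power at n = 15 with no period effect), and the period effect to 0.25, 0.5 or 1.0 SD.

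**The plan's own figure.** The 15 completers cannot be reproduced without an SD or power. At 25% drop-out, 15 completers need 15/0.75 = 20 starters. The stated 25 is a number screened, and this point does not depend on it.

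**Algebra.** Let D be formulation minus placebo, τ the formulation effect and π the change from period 1 to period 2. Then E(D) = τ − π for formulation first and τ + π for placebo first. With n1 and n2 completers in these sequences and n = n1 + n2:

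- bias of the paired mean = −π(n1 − n2)/n;
- expected squared SE of the paired test = [1 + 4π²·n1·n2/(n(n − 1))]/n, whereas the true squared SE is 1/n.

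At 8/7 the true SE is 1/√15 = 0.258. For π = 0.5 the paired test estimates √[(1 + 4 × 0.25 × 56/210)/15] = √(1.267/15) = 0.291. For π = 1.0 it estimates √(3.1/1.5 × 1/15) = √(2.067/15) = 0.371. The bias is only 1/15 = 0.067 of the period effect.

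**Simulation at 8/7** (at least 100,000 trials per case). Power has two columns because the small bias can help or hurt, depending on the sign of π and which sequence is larger.

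| Period effect (SD) | Type I error, paired | Power, bias favours formulation | Power, bias against formulation |
|---|---|---|---|
| 0.25 | 4.4% | 80% | 76% |
| 0.5 | 3.0% | 76% | 68% |
| 1.0 | 0.8% | 58% | 40% |

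The period-adjusted analysis averages the two sequence means of D and uses the pooled within-sequence variance on n − 2 degrees of freedom. It keeps type I error at about 5% and power at about 80% throughout. With no period effect its power at 8/7 is 79.5%, against 80.2% for the paired test.

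**Simulation at 10/5.** Bias = 5/15 × π, which is 0.17 SD for π = 0.5 and 0.33 SD for π = 1.0. Type I error is about 6% and 7%. With no period effect, adjustment costs about five power points (80% to 75%).

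**How likely each split is.** Suppose 20 children start, 10 per sequence, and 5 are lost at random. There are C(20,5) = 15,504 possible sets of losses.

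- 8/7 either way: 2 × 45 × 120/15,504 = 69.7%.
- 9/6 either way: 2 × 10 × 210/15,504 = 27.1%.
- 10/5 either way: 2 × 252/15,504 = 3.3%.

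At 9/6 with π = 0.5 the paired test is still conservative, with type I error about 4.1%.

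**The case against.** **No period effect is shown.** This stands. The article gives no period effect, and all sizes above are assumptions. A reader might infer that one is likely from "It is known in the AS population that there is a large placebo effect" in the Discussion, reasoning that placebo response should be strongest in the first period. The article says only that the effect is large, not that it fades, and the same paragraph says objective measures are prioritised. Ketosis, on which the sample size rests, is not obviously moved by expectation or by familiarity with testing. Familiarity with repeated EEG, ERP or gait testing would touch secondary safety measures, not the primary outcome of amount consumed against amount prescribed.

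**Serious bias needs an unlikely split.** This also stands for the overall comparison. A reader might infer that the test inflates false positives. At the likely splits it does the reverse. Inflation appears at 10/5, at about 3% under random loss. Uneven completion remains possible if drop-out depends on sequence, and small diet groups can easily be lopsided, because no numbers per diet are required and no stratification by diet is described. The article gives no evidence of sequence-related drop-out.

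**The paired test discards children with one period.** A reader might infer this too. For the primary analysis it is the population definition that excludes them, before any test is run, so a different test would not restore them.

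**The study is exploratory and a fuller plan may exist.** This limits the severity. It does not remove the point, because the article itself names the test.

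**Conclusion.** The stated test does not match the randomised design. That follows from the article alone and from exact algebra. The practical size is conditional. If there is no period effect, the paired test is valid and nothing is lost. If there is one, the likely result with 15 completers is a conservative test: at 8/7, power falls from about 80% to between 80% and 58% in one direction, or between 76% and 40% in the other, over period effects of 0.25 to 1.0 SD. Material bias needs a period effect and uneven completion together. The documents do not support saying that the formulation effect will be biased or that false positives will be inflated. The change should be made because it is cheap and protects against both outcomes, but the trial does not fail without it. The figures rest on normal differences with equal variance, a two-sided 0.05 test, and the assumed effect sizes.

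**What to change.** For formulation versus placebo, replace the paired t test with a crossover analysis: treatment and period as fixed effects, child as random effect, and small-sample degrees of freedom. For children with both periods this is the same as a two-sample comparison of within-child period differences between the two sequences, and the text could name that simpler form. Use the same analysis within diet groups where both sequences are represented.

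Children with one usable period can enter the model only in the intent-to-treat analysis. The primary set, as defined, requires both formulations and all assessments; changing that would be a separate decision. A period term does not alter the comparisons with baseline.

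No new data are needed. The cost is a change of wording and one degree of freedom: with no period effect, under one power point at 8/7 and about five at 10/5. If a separate analysis plan already specifies such a model, the article's sentence should be brought into line with it.

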Tolerability is determined at the end of each 4-week intervention period. Protocol compliance is monitored during both investigational and placebo intervention periods by recording the amount of formulation consumed. Formulation acceptability is assessed at the end of each intervention period by a parent questionnaire evaluating convenience, taste, and degree of acceptance of the nutritional formulation on a 10-point Likert scale or based on compliance with the study protocol and consumption of the formulation three times daily consistenty during the 4-week interventional period. Similar ranking systems to assess formulation acceptability have been used with other nutritional interventions in epilepsy populations [22–25].

Safety is assessed throughout the entire protocol period through (1) adverse event reporting and (2) assessment of clinical parameters collected throughout the protocol including anthropometrics, blood metabolism profile, dietary intake, seizure frequency, EEG, ERP, mobility, GI function, and sleep habits. In this population, the potential for negative effects of intervention must be closely monitored as patients are nonverbal. Additional file 4 contains details on collecting, assessing, reporting, and managing solicited and spontaneously reported adverse events.

Investigational and placebo formulations are administered with the serving size based on subject body weight. The investigational formulation provides beta-hydroxybutyrate, 2 g carbohydrate, 1 g protein, and 9 g fat, plus minerals, per 100 kcal. The placebo is matched for mineral content only. The formula is given orally as food or beverage three times per day.

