### Statistical considerations

The primary outcome of the trial is to assess the tolerability of a nutritional formulation containing BHB in patients with AS. Tolerability is demonstrated through patient compliance with the protocol as determined by the amount of formulation consumed as compared to the amount prescribed and is assessed at the end of each intervention period. Premature discontinuation of the nutritional formulation by the family is also deemed as potential intolerability. Tolerability is also assessed at the end of each intervention period through a parental questionnaire. These outcome measures were chosen as this is a vulnerable, nonverbal population with limited ability to communicate and, therefore, determining if the formulation is suitable and well tolerated is an appropriate first step.

The secondary outcomes include assessment of ketosis when consuming the nutritional formulation and safety of the nutritional formulation in patients with AS. Ketosis is evaluated daily through urine testing as well as blood analysis at the end of each intervention period. The degree and timing of ketosis may be clinically relevant to demonstrating better patient nutrition as nutritional ketosis has been related to better patient outcomes as described in the background of this manuscript. Safety is evaluated by changes in motor function, cognitive function, GI tolerance, sleep, and seizures, along with changes in height, weight, and blood metabolic panels as assessed at the end of each intervention period. In addition, adverse event reporting is monitored in real time by the study coordinator.

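### The set that decides the endpoints is defined by attendance rather than intake, so for ketosis it can drop a fully dosed child with complete ketone data and keep a low consumer unexamined

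*Protocol article*

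**What the plan says.** The article uses the idea of compliance in two ways.

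- **As an amount taken.** Under Procedures and interventions: "Protocol compliance is monitored during both investigational and placebo intervention periods by recording the amount of formulation consumed". Under Statistical considerations, the primary outcome, tolerability, is shown through "patient compliance with the protocol as determined by the amount of formulation consumed as compared to the amount prescribed". Early stopping counts too: "Premature discontinuation of the nutritional formulation by the family is also deemed as potential intolerability".
- **As membership of an analysis set.** Later in Statistical considerations: "any participant who received both protocol-required formulations and all required clinical assessments is considered protocol compliant". No amount is mentioned. The set has a decisive role: "Such an efficacy subset analysis will be the primary approach for determining whether the trial endpoints are met".

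A wider intent-to-treat set, covering any exposure to the formulation, is also defined but is not the primary approach. Ketosis is a secondary outcome, followed by daily urine tests and by blood at the end of each intervention period. The sample size nevertheless rests on it, through an assumed 100% change from baseline in "the minimal change of the secondary outcome, degree of ketosis". Procedures and interventions lists EEG, ERP and gait analysis as performed at each study visit.

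**The concern.** Whether a child has ketone values that can be analysed depends on the ketone measurements. Whether those values reflect the product depends on how much was taken. The rule for the deciding set looks at neither. It asks whether both formulations were received and whether every required clinical assessment was done.

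Two things follow for ketosis. Children with complete ketone data can be lost for reasons that have nothing to do with ketones. In a trial planned around 15 completers each loss counts, and children who cannot manage a gait or ERP session may not be a random subset. Children who took little are kept, which is defensible in itself, but the article describes no analysis that relates their ketone values to their intake. A weak ketosis result would then be reported without the one display that helps to explain it. Low intake is plausible here: the Background puts feeding problems at 75% in this population.

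**Working it through.** The article gives no expected intake and no count of missed assessments, so there is no stated figure to reproduce. The check compares the rule with the two meanings of compliance, then illustrates the stakes.

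**1. Servings.** Three per day ("The formula is given orally as food or beverage three times per day") over 4 weeks ("a 4-week period in which they receive nutritional formulation containing BHB or placebo"): 3 × 28 = 84 per period, 168 over both. Read literally, one serving of each formulation satisfies the receipt condition: 1/84 = 1.2% of a period's servings.

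**2. Two children under the stated rule.**

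| | Intake | Ketone data | Other assessments | In the deciding set? |
|---|---|---|---|---|
| Child A | 84 of 84 in both periods | complete | one gait or ERP session missed | No |
| Child B | low in both periods | complete | all done | Yes |

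This takes EEG, ERP and gait as required assessments, since they are scheduled at each visit; the schedule figure itself is not available. Child A is the more informative child for ketosis on either meaning of compliance that involves amount, and is the one excluded.

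**3. Cost of losing children like A.** Assumptions, not in the article: two-sided paired t test at 0.05, 15 children with complete ketone data, standardized effect d. Power from the noncentral t with noncentrality d√n:

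| d | n = 15 | n = 14 | n = 13 | n = 12 |
|---|---|---|---|---|
| 0.6 | 0.580 | 0.547 | 0.512 | 0.475 |
| 0.78 | 0.802 | 0.770 | 0.733 | 0.692 |
| 1.0 | 0.949 | 0.932 | 0.911 | 0.883 |

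**4. Effect of keeping children like B.** Assume that the ketone rise is proportional to intake and that the other children take everything.

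- 1 of 15 at zero intake: 14/15 = 93% of the true rise.
- 3 of 15 at zero: 12/15 = 80%.
- 5 of 15 at zero: 10/15 = 67%.
- 5 of 15 at 25% intake: (10 × 100% + 5 × 25%)/15 = 75%.

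With a fraction f of responders, the diluted standardized effect is d·f/√(1 + d²f(1 − f)). For 3 of 15 at zero, f = 0.8, and power with n = 15 falls from 0.58 to 0.39 (d = 0.6), 0.80 to 0.57 (d = 0.78) or 0.95 to 0.76 (d = 1.0). The shift is toward no effect.

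**5. What an intake floor would do to tolerability.** Suppose 12 of 15 children take 95% and 3 take 1/84. Mean intake is (12 × 0.95 + 3 × 1/84)/15 = 0.762. A floor that removes the three gives 0.95. The primary outcome improves only because the children who did not tolerate the product were removed.

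**The case against.** **A stronger reading.** A reader might infer that the deciding set needs an intake floor throughout, and that counting a child with 1 of 84 servings as compliant spoils the endpoint results. The documents do not support this.

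- The primary outcome is intake. For tolerability a near-refuser must stay in, and step 5 shows the harm of a floor.
- The article nowhere says that the set is meant to select on dose. That is an inference from its label.
- It would be wrong to say that the trial cannot separate a product that fails to raise ketones from one that was not swallowed. Intake is recorded in both periods and ketones are measured daily and at period end. What is missing is a described analysis that joins them.
- The 1-of-84 child is a literal extreme. Willingness to consume the formulation is an inclusion criterion, and families are telephoned weekly.
- Ketosis under the formulation as prescribed is a legitimate question. An intake-restricted set selects after randomisation and, if applied to both periods, would drop a child who took all the active product but refused placebo. It belongs in a supportive role.

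All of this stands.

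**Two further defences.** Receipt might mean receipt as required, and a numerical threshold may sit in the full protocol or SAP. The first is possible, but the same section uses the same verb for exposure of any duration in the intent-to-treat definition. The second is fair, and the absence of a threshold is not criticised here. Neither explains why an unrelated missed assessment should remove a child from the ketosis analysis: that condition is written out in the article.

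**Conclusion.** The concern holds in a limited form. The definition of the deciding set does not match the article's own intake-based meaning of compliance, and for ketosis it selects on completeness of unrelated assessments. It can exclude a fully dosed child with complete ketone values while including low consumers, with no intake-related ketosis analysis described.

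The outcome affected is secondary, in an exploratory trial, but the sample size was built on it. Keeping low consumers biases toward no effect, so it costs power and clarity and does not create a false positive. The size of any dilution cannot be derived from the article; the 75% and 67% figures and all the power values rest on assumed intake, a proportional response and assumed standardized effects. That low consumers stay in the tolerability analysis is correct. The same rule, however, also removes children who stop before receiving both formulations, whom the article treats as potentially intolerant, and they should be kept for that outcome as well.

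The point is worth acting on because it can be fixed before unblinding at almost no cost.

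**What to change.** 1. **Ketosis, main analysis.** Include every treated child with the relevant ketone measurements in both periods. Do not require EEG, ERP, gait or other unrelated assessments.
2. **Ketosis, supportive analysis.** Relate ketone values to the recorded ratio of consumed to prescribed amount, with an individual plot. Optionally add a subset above an intake threshold fixed before unblinding. Label this an as-dosed estimate.
3. **Tolerability.** Apply no intake floor. Keep low consumers and early stoppers.
4. **Wording.** Reconcile the two uses of compliance in the article, so that the term for the amount taken is not also the name of a set defined by attendance.

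Cost: a wording change and slightly more analysis work, with no new data collection. The analysis sets will differ by endpoint, which must be stated clearly in the report.

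### Primary tolerability is decided in a protocol-compliant subset that leaves out children who stop before receiving the second product or who withdraw and miss an assessment, which tilts the result towards good tolerability

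*Protocol article*

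**What the plan says.** All the relevant text is in the Protocol article under Statistical considerations.

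- **Primary outcome:** "The primary outcome of the trial is to assess the tolerability of a nutritional formulation containing BHB in patients with AS".
- **How it is measured:** "Tolerability is demonstrated through patient compliance with the protocol as determined by the amount of formulation consumed as compared to the amount prescribed", at the end of each intervention period, together with a parental questionnaire.
- **Stopping early:** "Premature discontinuation of the nutritional formulation by the family is also deemed as potential intolerability".
- **Broad population:** "Any patient who receives the study formulation for any amount of time will be included in the intent-to-treat population for study analyses". Missing data in this population are only to be taken up when results are discussed.
- **Narrow population:** "any participant who received both protocol-required formulations and all required clinical assessments is considered protocol compliant".
- **Which one decides:** "Such an efficacy subset analysis will be the primary approach for determining whether the trial endpoints are met". No exception is made for tolerability, and nothing elsewhere in the article assigns tolerability to the broad population.

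**The concern.** The same event has two roles. In the outcome definition, stopping the formula is evidence about tolerability. In the population rule, stopping removes the child from the deciding analysis whenever the second product is then never received or a required assessment is missed. Those children probably tolerated the product less well than the children who remain, so the result for the active formula is pushed upwards.

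The word compliance also changes meaning. In the outcome definition it is the share of the prescribed amount consumed. In the population rule it is receipt of both products plus attendance at assessments, with no intake threshold. A child who consumed very little but attended everything counts as compliant. A child who consumed everything but missed one required assessment does not.

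At stake is the main conclusion of the trial. Tolerability was chosen because these children cannot report difficulties themselves, and a family's decision to stop is one of the clearest signals available.

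**Working it through.** **Inputs.** From Statistical considerations: 25% drop-out, 25 screened, 15 completers ("Considering a 25% drop-out rate, an estimate of 25 subjects need to be screened to achieve 15 completers"). From Study design: two sequences, allocated 1:1. The article gives no reasons for drop-out and no cut-off for calling a child tolerant, so both are treated as assumptions below.

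**The plan's own figure.** Starters needed for 15 completers at 25% drop-out: 15/(1 − 0.25) = 20. The forward check from 25 gives 25 × 0.75 = 18.75, not 15. The figure of 25 fits only if 1 − 20/25 = 20% are also lost between screening and start, which the article does not state. This point does not depend on the 25; it uses 20 starters and 5 drop-outs, which are derived.

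**Who leaves the deciding analysis.**

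| Course of the child | Deciding subset | Any-exposure population |
|---|---|---|
| Stops in period 1, never receives second product | Out | In |
| Receives both, withdraws, misses a required assessment | Out | In |
| Stops partway through a period, receives both products, attends all required assessments | In, with low intake | In |
| Consumes little, receives both, attends all | In | In |

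**Size for a tolerated/not-tolerated summary.** Let k of the 5 drop-outs be due to intolerance of the active formula, with all 5 excluded from the subset. Assume that every other child tolerates the formula. The subset then shows 15/15 = 100% (exact 95% CI 78.2% to 100%) whatever k is. If all 20 starters received the active formula, the any-exposure figure is (20 − k)/20:

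- k = 0: 100%, gap 0 points
- k = 1: 95%, gap 5 points
- k = 3: 85%, gap 15 points
- k = 5: 75% (exact 95% CI 50.9% to 91.3%), gap 25 points

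**Effect of placebo-first drop-outs.** A child who stops during a first period on placebo never took the active formula and does not belong in its denominator. If the other 5 − k drop-outs are all of this kind, the figure is 15/(15 + k). For k = 1 it is 15/16 = 93.75% (gap 6.25 points), for k = 3 it is 15/18 = 83.3% (gap 16.7 points), and for k = 5 it is again 75%. The range remains 0 to 25 points.

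**Size on the intake scale.** Assume that children who do not stop for intolerance consume 90% of the prescribed amount and those who do stop consume 10% to 50%. The subset shows 90%. All 20 starters show [90 × (20 − k) + m × k]/20, with m the intake percentage of those who stop:

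- k = 1: 86% to 88%
- k = 3: 78% to 84%
- k = 5: 70% to 80%

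**The case against.** The best defence is that the broad population is defined in the same paragraph, and that the narrow one is labelled an efficacy subset, which might not be meant to cover tolerability. The first part is true but does not help, because the broad population is not the one that decides. The second part shows that the text could be read more kindly. Even so, the deciding sentence refers to the trial endpoints without exception, and the named endpoints are tolerability, ketosis and safety.

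Several stronger readings are tempting, and the article does not support them:

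- **That early stopping can never appear in the primary analysis.** The rule asks that both products were received, not that both periods were completed. The third row of the table above is a child who stops early and stays in.
- **That children with adverse events disappear from safety reporting.** Procedures and interventions has safety assessed over the whole protocol period, adverse events are monitored in real time, and there is a data safety monitoring board. Nothing confines adverse event reporting to the subset. What the rule can reach is the verdict on the safety endpoint, mainly its end-of-period change measures.
- **That a child who cannot complete EEG, ERP or gait analysis is dropped.** These are performed at each study visit, but the article text does not say which assessments count as required for compliance, or whether an attempted one suffices. It is a possibility, not a fact.
- **That 25 points is the expected bias.** It is an upper bound.
- **That every stop is intolerance.** The plan says only potential intolerability, and families may withdraw for any reason. Counting every stop as a failure without qualification could bias the result against the product.

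The study is also described as exploratory and sets no tolerability threshold. That lowers the stakes of a formal verdict but does not reconcile the two rules.

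**Conclusion.** The point stands in a bounded form. The outcome definition and the deciding population conflict: some children whose stopping is itself outcome information are excluded from the analysis that settles the primary outcome. The bias in the active formula's tolerability figure is favourable, provided that the excluded children tolerated it less well than those retained. It runs from 0 to at most 25 percentage points under the plan's own 25% drop-out. The upper end needs all five drop-outs to be active-formula intolerance and all to fall outside the subset; it is 0 if none are related to the active formula. For the comparison with placebo the direction is less certain, because children who stop during a first period on placebo are removed too. The differing meanings of compliance are a separate inconsistency that follows directly from the text.

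**What to change.** 1. Make the any-exposure population decisive for tolerability and for the safety endpoint, analysed by the product received in each period.
2. Compute intake against the full amount prescribed for the period, with intake after a stop counted as zero.
3. Report premature discontinuations by product and by reason, with 95% confidence intervals, counted as potential intolerability. Add a sensitivity analysis that excludes stops clearly unrelated to the product.
4. Keep the protocol-compliant subset as supportive, for example for ketosis. The paired t test needs data from both periods, so it cannot carry the tolerability decision alone; the by-product summaries should.
5. Do not make inclusion in the tolerability analysis depend on completing unrelated assessments, and use separate terms for intake-based compliance and protocol completion.

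The cost is a change of wording in Statistical considerations. The amount consumed is already recorded, so no new data are needed. The tolerability figure may look less favourable.
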